## Abstract

**Background:**

Kidney transplant recipients present reduced physical function and a high prevalence of cardiometabolic complications, which increase cardiovascular risk and compromise long-term graft outcomes. Resistance training has demonstrated beneficial effects in this population; however, previous interventions have shown heterogeneity in load prescription and have not incorporated objective monitoring of movement velocity. Velocity-based resistance training (VBT) allows precise regulation of exercise intensity and fatigue, potentially improving the safety and individualization of exercise prescription in clinical populations.

**Objective:**

This study aims to evaluate the effects of a 12-week VBT program on renal function and metabolic health in kidney transplant recipients and to compare 2 different load-control strategies based on movement velocity.

**Methods:**

This pilot randomized controlled trial will include adult kidney transplant recipients with stable graft function. Participants will be randomly assigned (1:1) to either a maximal velocity group, in which sets will be terminated at a 20% velocity loss threshold, or a constant submaximal velocity group, in which participants will perform repetitions at 50% of the participant’s individual maximal velocity. Both groups will complete 3 supervised training sessions per week for 12 weeks with real-time velocity monitoring. Primary outcomes will include renal and metabolic health domains assessed through venous blood analysis. Serum creatinine will be the prespecified hierarchical primary renal end point, and high-density lipoprotein cholesterol will be the prespecified hierarchical primary metabolic end point. Estimated glomerular filtration rate will be calculated using the Chronic Kidney Disease Epidemiology Collaboration equation. Secondary outcomes will include blood pressure, body composition, muscular strength, metabolic syndrome criteria, and the force-velocity profile. Data will be analyzed using analysis of covariance and linear mixed-effects models following a predefined hierarchical inferential strategy.

**Results:**

The study was initiated in September 2025. Participant recruitment and the intervention phase have been completed. All 14 participants completed the 12-week training program, and no participants were lost to follow-up. Preintervention and postintervention data collection has been completed according to the study protocol. The study database has been cleaned and locked, and statistical analyses are currently underway. Publication of the primary study results is anticipated in late 2026.

**Conclusions:**

This study introduces the implementation of VBT in kidney transplant recipients. The findings are expected to provide evidence on the feasibility and potential benefits of this approach and may support the integration of exercise professionals into multidisciplinary transplant care teams.

**Trial Registration:**

ClinicalTrials.gov NCT07370727; https://clinicaltrials.gov/study/NCT07370727

**International Registered Report Identifier (IRRID):**

DERR1-10.2196/94010

## Introduction

Kidney transplantation is the treatment of choice for patients with end-stage chronic kidney disease, as it significantly improves survival and quality of life compared with dialysis [1,2]. However, despite these benefits, kidney transplant recipients continue to present a high risk of metabolic and cardiovascular complications that negatively affect long-term graft and patient survival [3,4]. These complications are closely associated with modifiable factors, such as physical inactivity, increased adiposity, insulin resistance, and the presence of metabolic syndrome, the prevalence of which is considerably elevated in this population [5-7]. Metabolic syndrome has been associated with an increased risk of graft dysfunction, cardiovascular events, and mortality, highlighting the importance of implementing interventions aimed at improving metabolic and functional health in kidney transplant recipients [8,9].

In this context, physical exercise has been recognized as a safe and effective intervention for improving physical fitness, body composition, quality of life, and several cardiometabolic markers in kidney transplant recipients [10-13]. Evidence derived from randomized controlled trials and systematic reviews has demonstrated that structured exercise programs can improve muscular strength, cardiorespiratory capacity, and certain cardiovascular risk factors without compromising graft function when appropriately supervised [10,11,14-16]. In particular, resistance training has shown positive effects on muscle mass, insulin sensitivity, and metabolic health, which are key factors in the clinical prognosis of this population [12,14].

Nevertheless, despite these benefits, the results of intervention studies have been heterogeneous and inconsistent, particularly with respect to metabolic and renal outcomes. One of the main limitations explaining this inconsistency is the lack of standardization in the programming and periodization of resistance training load components. Recently, a scoping review that characterized resistance training programs in kidney transplant recipients identified substantial heterogeneity in critical variables, such as intensity, volume, number of sets, repetitions, and recovery intervals, with a predominance of prescribing intensity based on a percentage of 1-repetition maximum as the primary method [17]. This methodological heterogeneity limits the reproducibility of interventions and hinders the identification of optimal resistance training prescription models for this clinical population.

Importantly, this review also reported that movement velocity, a key variable for the precise control of intensity and neuromuscular fatigue, has not been considered a central component of resistance training programming for kidney transplant recipients [17]. Movement velocity is one of the most valid and sensitive indicators for load prescription in resistance training, allowing the estimation of relative intensity from the first repetition, the control of fatigue through monitoring of velocity loss, and the optimization of neuromuscular and metabolic adaptations [18-21]. The absence of this variable in previously studied resistance training programs represents a critical limitation, particularly in clinical populations in which individualization and precise stimulus control are essential.

Over the last decade, velocity-based resistance training (VBT) has emerged as an innovative paradigm that enables individualized, objective, and precise prescription of training load [18-21]. This approach allows real-time adjustment of intensity, control of effective training volume, and optimization of training safety and efficacy, characteristics that are particularly relevant in clinical populations such as kidney transplant recipients.

However, to date, no randomized controlled trials have evaluated the effects of a resistance training program prescribed and monitored using movement velocity on renal function and metabolic health in kidney transplant recipients. This lack of evidence represents a critical gap in the scientific literature, especially considering the previously documented heterogeneity in the periodization of load components and the absence of objective intensity control in this population [17].

Although serum creatinine is widely used as a clinical marker of renal function in kidney transplant recipients, its interpretation in the context of resistance training requires caution. Increases in skeletal muscle mass induced by training may lead to elevations in serum creatinine independent of changes in renal function. Despite this limitation, creatinine remains a clinically relevant and routinely monitored biomarker in this population. Therefore, its inclusion as a primary renal outcome is justified, but results will be interpreted alongside complementary indicators and within the context of potential training-induced muscular adaptations. In addition, high-density lipoprotein cholesterol (HDL-C) was selected as the primary metabolic outcome because of its sensitivity to exercise interventions and its established role as a protective cardiovascular factor in transplant recipients.

Therefore, this study aims to describe the protocol for a pilot randomized controlled trial designed to evaluate the preliminary effects of a VBT program on renal function and metabolic health in kidney transplant recipients. In addition to assessing preliminary efficacy, this pilot trial aims to evaluate feasibility indicators, including the recruitment rate, intervention adherence, and safety profile. The findings of this study are expected to provide foundational evidence to inform the design of future adequately powered randomized controlled trials in this clinical population.

## Methods

### Study Design

This study is designed as a pilot randomized, parallel-group controlled clinical trial with a 1:1 allocation ratio to assess the feasibility, safety, and preliminary efficacy of 2 VBT strategies in kidney transplant recipients. The pilot nature of the trial aims to generate preliminary estimates of effect size and variability to inform future adequately powered randomized controlled trials in this population. The protocol has been developed in accordance with the SPIRIT (Standard Protocol Items: Recommendations for Interventional Trials) guidelines to ensure methodological rigor, transparency, and reproducibility [22]. A completed SPIRIT 2025 checklist is provided as Multimedia Appendix 1.

### Feasibility Outcome

Feasibility outcomes will include recruitment rate, intervention adherence, retention rate, safety, and data completeness. Recruitment will be considered successful if at least 2 participants per month are enrolled, considering the clinical characteristics and limited availability of the target population. Adherence will be defined as attendance at ≥80% of the scheduled sessions. Retention will be considered acceptable if ≥85% of participants complete the intervention. Safety will be assessed through monitoring of adverse events, with an acceptable threshold defined as <10% of participants experiencing exercise-related complications. Data completeness will be considered adequate if ≥90% of the expected data are collected.

### Ethical Considerations

This study was approved by the research ethics committee of the Fundación Universitaria del Área Andina (approval no. 15; dated April 22, 2025) and will be conducted in accordance with the ethical standards of the institutional research committee and the principles of the Declaration of Helsinki. Furthermore, the trial protocol was prospectively registered at ClinicalTrials.gov (National Library of Medicine) under the identifier NCT07370727, ensuring transparency, traceability, and public access to study information.

All participants will be fully informed about the study procedures, potential risks, and benefits, and will provide written informed consent prior to enrollment. Participation will be voluntary, and participants may withdraw from the study at any time without consequence. Participant confidentiality will be ensured by assigning anonymized identification codes and storing data in secure, password-protected databases accessible only to the research team. No personal identifiers will be disclosed in any publication derived from this study. Participants will not receive financial compensation but will benefit from supervised exercise sessions and health monitoring throughout the intervention.

### Participants and Eligibility Criteria

Men and women aged 18 to 50 years with a history of kidney transplantation and who are at least 12 months after transplantation will be invited to participate, provided they have stable graft function during the previous 6 months. Stable graft function will be defined as resting serum creatinine levels below 1.5 mg/100 mL, an estimated glomerular filtration rate of ≥60 mL/min/1.73 m², no variation greater than +10% to –10% in renal function over the previous 3 months, the absence of acute rejection episodes in the last 6 months, no recent changes in immunosuppressive therapy, and proteinuria levels below 300 mg/g. All participants will be required to have written medical clearance from their treating nephrologist authorizing participation in moderate to vigorous physical exercise and to sign informed consent prior to inclusion in the study. Individuals with active autoimmune disorders, a recent history (≤6 months) of coronary artery disease, osteomuscular limitations that could prevent safe participation in the intervention, a diagnosis of diabetes mellitus before or after transplantation, active infection, or use of immunosuppressive agents requiring exercise restriction, such as mechanistic target of rapamycin inhibitors, at the time of enrollment will be excluded. Recruitment will be conducted through a public call distributed by the *Asociación Colombiana de Deportistas Trasplantados*, followed by an initial telephone screening. Potentially eligible participants will subsequently be invited to an in-person evaluation, during which clinical history will be obtained, eligibility criteria will be verified, and informed consent will be obtained.

### Sample Size

The sample size was estimated based on the primary outcome domains of the study, corresponding to renal function and metabolic health, specifically changes in serum creatinine and HDL-C. The calculation was informed by evidence from previous supervised exercise interventions in kidney transplant recipients that reported clinically meaningful changes in these physiological parameters [10,16,23]. Considering the exploratory nature of this pilot trial, the sample size was not primarily determined to test hypotheses or detect statistically significant between-group differences. Rather, a pragmatic approach was adopted to include 14 participants (7 participants per group), which was considered sufficient to evaluate key feasibility outcomes, such as recruitment, adherence, retention, and safety, as well as to provide preliminary estimates of variability and effect size. These estimates are intended to inform the design and sample size calculation of a future fully powered randomized controlled trial. Therefore, any between-group comparisons conducted in this study will be considered exploratory and interpreted with caution. The calculation was performed using the Power and Sample Size Calculation software (Vanderbilt University).

### Randomization and Allocation Concealment

Participants will be assigned to intervention groups using a block randomization procedure with a 1:1 allocation ratio, generated through a computerized random sequence generator. To ensure allocation concealment, a centralized online randomization platform (Research Randomizer, Social Psychology Network) will be used, to which only the methodological coordinator will have access. This coordinator will not be involved in outcome assessment or data analysis. After eligibility criteria are confirmed, informed consent is obtained, and baseline assessments are completed. Participant information will be entered into the platform, which automatically assigns participants to 1 of the 2 intervention groups using an encrypted system, ensuring allocation unpredictability and minimizing selection bias.

### Blinding

Due to the nature of the intervention, blinding of participants and trainers will not be possible. However, a single-blind design will be implemented for outcome assessors and data analysts. Evaluators responsible for biochemical, anthropometric, and physiological measurements will remain blinded to group allocation, and statistical analysis will be conducted using a coded dataset in which groups will be identified as group A and group B. This procedure will minimize measurement and analysis bias, strengthening the internal validity of the study.

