### Intervention: Training Protocols

The VBT program will be conducted over 12 weeks, with 3 weekly sessions on nonconsecutive days, totaling 36 sessions. Each session will last approximately 50 to 80 minutes and will include warm-up, main training, and cool-down phases. Exercises will include bench press, half squat, and military press, performed on a Smith machine, with velocity monitored using a linear encoder.

Participants will be randomly assigned to 1 of 2 intervention groups. Group A—maximal velocity with velocity loss control: participants will perform the concentric phase at maximal voluntary velocity and the eccentric phase in a controlled manner. Sets will be terminated when mean propulsive velocity decreases by 20% relative to the fastest repetition in the set. The load will be progressively increased following the principle of progressive overload. The detailed load progression and training parameters for the maximal velocity group are presented in Table 1.

**Table 1 table1:** Load progression and training parameters for the maximal velocity group.

Sessions	Intensity (% 1-repetition maximum)	Sets per exercise	Termination criterion (% velocity loss)	Rest between sets (minutes)	Rest between exercises (minutes)
1-6	20	2	20	1	3
7-12	30	2	20	1	3
13-18	40	3	20	2	3
19-24	50	3	20	2	3
25-36	60	4	20	2	3

Group B—constant submaximal velocity training: participants in this group will perform the same exercises, with identical load progression, number of sets, and recovery periods. However, repetitions will be performed at a concentric velocity equivalent to 50% of the previously determined individual maximal velocity, eliminating the relative velocity loss criterion as the indicator for set termination. In this group, training volume will be standardized using a fixed number of repetitions per set. The detailed load progression and training parameters for the maximal velocity group are presented in Table 2.

**Table 2 table2:** Load progression and training parameters for the constant submaximal velocity group.

Sessions	Intensity (% 1-repetition maximum)	Repetitions per set	Sets per exercise	Rest between sets (minutes)	Rest between exercises (minutes)
1-6	20	30	2	1	3
7-12	30	25	2	1	3
13-18	40	20	3	2	3
19-24	50	18	3	2	3
25-36	60	15	4	2	3

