This study has several strengths. First, it adopts a randomized controlled design, which enhances internal validity. Second, it incorporates an objective and innovative method for training-load prescription through velocity-based monitoring. Third, it targets a specific clinical population for which evidence regarding optimized resistance training strategies is limited. However, several limitations must be acknowledged. As a pilot randomized controlled trial, the sample size is small and not intended to provide definitive evidence of effectiveness. Therefore, findings related to between-group differences should be interpreted with caution. Additionally, the inability to blind participants and trainers may introduce performance bias, although efforts have been made to minimize this through blinded outcome assessment and data analysis. Finally, the single-center nature of the study may limit the generalizability of the findings.

The findings of this pilot study are expected to inform the design of a future fully powered randomized controlled trial. Future research should consider larger sample sizes, multicenter designs, and longer follow-up periods to evaluate the long-term effects of VBT on renal function, metabolic health, and clinical outcomes in kidney transplant recipients. Additionally, further studies may explore the integration of VBT with other lifestyle interventions, such as nutritional strategies, to optimize patient outcomes.

The results of this study will be disseminated through publication in peer-reviewed scientific journals and presentations at national and international conferences in the fields of sports science, rehabilitation, and clinical exercise physiology. Additionally, findings will be shared with health care professionals and relevant institutions involved in the care of kidney transplant recipients, with the aim of contributing to evidence-based exercise prescription in this population.

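### As described, the analyst is not blinded: the coded dataset uses the letters A and B, which the protocol itself assigns to the two regimens

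*Protocol article*

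**What the plan says.** The Blinding section accepts that participants and trainers cannot be masked and states instead that "a single-blind design will be implemented for outcome assessors and data analysts". For the analyst it names one device: "statistical analysis will be conducted using a coded dataset in which groups will be identified as group A and group B". It then claims a benefit: "This procedure will minimize measurement and analysis bias, strengthening the internal validity of the study". The Discussion relies on the same safeguard when it weighs the unmasked participants and trainers, saying that "efforts have been made to minimize this through blinded outcome assessment and data analysis".

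The section Intervention: Training Protocols names the arms "Group A—maximal velocity with velocity loss control" and "Group B—constant submaximal velocity training".

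**The concern.** A code masks the analyst only if the analyst cannot translate it. Here the two code letters are also the published names of the arms, and a trial analyst has to know the protocol. Followed literally, the procedure gives the analyst a dataset with the treatment named.

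What is at stake is a stated safeguard. With participants and trainers unmasked, masked assessment and masked analysis are the two protections that the protocol offers, and it cites the second both in the Blinding section and in the Discussion. A reader of the results paper would credit the trial with analyst blinding that the described procedure does not deliver. Any analytic judgement still open would then be made with the arms known.

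**Working it through.** No arithmetic applies, so the check sets the statements side by side.

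| Step | Where | What it establishes |
|---|---|---|
| 1 | Blinding | Data analysts are claimed to be masked |
| 2 | Blinding | The means is a dataset whose arm labels are A and B |
| 3 | Intervention: Training Protocols | "Group A—maximal velocity with velocity loss control: participants will perform the concentric phase at maximal voluntary velocity" |
| 4 | Intervention: Training Protocols | "Group B—constant submaximal velocity training: participants in this group will perform the same exercises" |
| 5 | Randomization and Allocation Concealment | The methodological coordinator takes no part in outcome assessment or analysis, but is not said to code the dataset |

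**Do the labels coincide?** Yes. The dataset labels {A, B} and the regimen labels {A, B} are identical.

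**Does anything break the link between them?** No section says that the dataset letters were drawn separately from the regimen names. Step 5 identifies someone who could hold a key, but does not give that person the task.

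**What decides the matter in practice?** How the letters were assigned.
- If they were carried over from the regimen names, the analyst can decode every row.
- If they were drawn at random for the dataset, they would agree with the published letters half the time by chance (1 of 2 possible assignments), and the letter alone would tell the analyst nothing reliable.

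The article does not say which of these happened.

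**How much could an unmasked analyst influence?**
- *Primary model:* Statistical Analysis fixes an ANCOVA of the post-intervention value on group and baseline. There is little room here.
- *Order of testing:* creatinine comes first, then the metabolic domain with HDL-C, which Outcome Measures names as its primary marker. This is fixed.
- *Measurement:* both endpoints come from a certified laboratory (Instruments and Procedures). Knowledge of the arm at the analysis stage does not alter them.
- *Missing data:* Results reports that all 14 participants completed the programme, that 0 of 14 were lost to follow-up, and that data collection before and after the intervention is complete. An open choice of imputation method has little to act on.
- *Mean or median:* this rule governs descriptive display and leaves the between-group test unchanged.
- *What remains:* the content of the sensitivity analyses, and the construction of the composite metabolic and strength indices. The article may properly leave such detail to a fuller document. They are listed only to show where judgement might still enter.

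**The case against.** The strongest reply is that A and B are generic masking labels. The word coded suggests that a code exists, and nothing states that A in the dataset is A in the training section. A condensed article also commonly omits who holds the key and when it is opened. Much of this stands. The letters may have been assigned independently, and the missing key-holder and unmasking time are not faults in themselves. What does not fall away is that the article states a mechanism and, within the same Methods section, publishes what its labels stand for.

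A reader might go on to infer several stronger things that the documents do not support:

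- *That the analyst was in fact unblinded for every comparison.* The text shows only that masking is not achieved as described.
- *That the session records reveal the arm.* Repetitions and velocity do differ by design, but no section says that these records are in the analysis file. They are neither listed as outcomes nor entered in the models.
- *That with 7 per arm, altering a single value could turn the result.* No calculation supports this. Statistical Analysis describes no transformation or removal of values, and the database is reported as cleaned and locked.
- *That imputation choices would be made with the arms known.* Full completion leaves almost nothing to impute.

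It is also fair to say that between-group comparisons are declared exploratory (Sample Size), which lowers the stakes.

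**Conclusion.** The point holds in limited form. As described, analyst blinding is not achieved, because the masking labels are the published names of the arms and nothing says that the two were assigned independently. The Blinding section and the Discussion therefore claim a protection that the stated procedure does not provide.

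The size of any bias cannot be given. For creatinine and HDL-C it is probably small, for the reasons set out in the working. Masking of outcome assessors is a separate matter and is untouched.

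The conclusion assumes that the analyst has access to the protocol and that the dataset letters were taken from it. The first is close to certain. The second is the natural reading but unconfirmed, and if it is wrong the remedy is a clarifying sentence. The point deserves correction because an inaccurate blinding statement would pass into the results paper. It is not a reason to doubt the primary analysis.

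**What to change.** 1. **Establish the facts first.** Ask the sponsor who assigned the dataset letters and by what method.
2. **If they were assigned independently of the regimen names,** say so in the Blinding section and the results paper. Nothing else is needed.
3. **If they match the regimen names,** have someone outside the analysis, for example the methodological coordinator, replace them with randomly assigned neutral labels that appear nowhere in the protocol. That person holds the key until the creatinine and HDL-C output is final.
4. **Where analyses have already been run under matching letters,** recoding cannot restore masking for those analyses. Withdraw the analyst-blinding claim in the Blinding section and the Discussion, and report that the analyst was not effectively blinded. The claim about outcome assessors can stay.
5. **As a precaution,** keep any session-level training data out of the blinded analysis file.

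Suggested wording where recoding is still possible: *The analysis dataset will carry neutral arm codes, assigned at random by the methodological coordinator and not used elsewhere in the protocol; the coordinator will release the key once the creatinine and HDL-C analyses are final.*

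Recoding takes minutes and does not affect the analysis itself. Its value depends on timing, because Results says that the database is locked and analyses are under way. If it comes too late, the cost is a corrected statement in two places and a sentence in the results paper.
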